### 2.5. Withdrawal and Replacement of Study Subjects

Study subjects may withdraw from the study at any time, with or without providing a reason, without incurring any penalty or adverse consequences. Participants may revoke their consent at any time without the obligation to justify their decision and without any resulting liability or detriment. Subjects who withdraw from the study will not undergo further follow-up and will not be replaced. The investigator reserves the right to withdraw a subject from the study if it is determined that the subject can no longer comply with all study requirements or if any study procedures are deemed potentially harmful. Data collected up to the point of withdrawal will be retained and included in the analysis; however, no additional data will be gathered from the subject following withdrawal.

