### 2.6. Withdrawal Criteria

Subjects will be withdrawn from this study if any of the following criteria are met:The occurrence of an adverse event which, in the judgment of the investigator, necessitates the withdrawal of the subject.A protocol deviation that compromises the interpretation of the study results and the scientific validity of the study.The voluntary decision of the subject.The explicit refusal of the subject to continue his/her participation in the study.Loss to follow-up.

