### 2.10. Intervention

Upon consenting to participate, patients will be randomized into two study arms based on the intervention administered:Control Group: Patients will receive modifications to their pharmacological treatment alongside standard nutritional recommendations. The control group will follow a Mediterranean diet with increased caloric and protein intake during the acute flare. The diet will emphasize a balanced nutritional intake without unnecessary food restrictions, along with adequate fiber and hydration (as tolerated), and a reduction in ultra-processed food consumption.Experimental Group: Patients will receive modifications to their pharmacological treatment and will be assigned to an intervention consisting of an exclusion diet in conjunction with supplemental enteral nutrition. This nutritional strategy will involve a progressive increase in the caloric intake derived from the diet, coupled with a corresponding reduction in supplemental enteral nutrition.

Prior to initiating the nutritional intervention—and subsequently at 6 and 12 weeks after the onset of the diet—alterations in body composition and functionality will be evaluated through anthropometric measurements and biochemical parameters pertinent to both the underlying pathology and the overall health status of the patient. Comprehensive functional assessments, including dynamometry and additional analyses such as BIA and nutritional ultrasound, will be conducted. Furthermore, a detailed nutritional and morphofunctional evaluation will be performed 24 and 48 weeks after the initiation of the exclusion diet [Figure 1].

Baseline biological samples (blood, urine, and stool specimens) will be collected before the start of the nutritional intervention. During the intervention, additional collections will occur at the 6-, 12-, 24-week visits, with a final sample collection at 48 weeks. A detailed assessment schedule can be found in Table 1.

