### 2.12. Randomization and Blinding

Patients will be randomized in a 1:1 ratio after meeting the study inclusion and exclusion criteria. In the control group, patients will receive standard nutritional recommendations, whereas in the intervention group, they will follow a dietary strategy based on partial enteral nutrition combined with an exclusion diet, which has been shown to be effective in inducing remission, promoting mucosal healing, and serving as a rescue therapy for patients with inadequate response to biologic treatments.

Patients in the intervention group will be required to maintain this dietary strategy for 12 weeks, with structured follow-up visits at 6, 12, 24, and 48 weeks. Subsequently, patients should continue with the maintenance phase starting from week 13 onwards. Nutritional intake will be adjusted to ensure a balanced provision of macronutrients and essential micronutrients, prioritizing the inclusion of key substrates for short-chain fatty acid production while avoiding foods and additives with potential pro-inflammatory effects.

Simple randomization will be computer-generated and conducted by a member of the research team at the study site. Due to the nature of the intervention, neither patients nor research or medical staff will be blinded. Group assignment will be disclosed to patients at the moment of their participation acceptance.

Furthermore, to minimize the risk of bias, the clinicians from the Gastroenterology Department responsible for performing imaging assessments, as well as the translational researchers from the Biomedical Research Institute of Murcia (IMIB) in charge of analyzing blood, urine, and stool samples, will remain blinded to the dietary allocation of the study participants.

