## 3. Discussion

The findings of this study could contribute to the implementation of nutritional therapy in adult patients with active luminal CD (non-stricturing, non-penetrating) of the small intestine, with or without colonic involvement, who are initiating treatment with biologic agents or JAK inhibitors. Partial enteral nutrition (PEN) combined with the exclusion diet (ED) has demonstrated efficacy in inducing remission in both pediatric and adult patients, promoting mucosal healing and serving as a rescue therapy for patients who fail biologic therapy [11,12].

In this context, the Crohn’s Disease Exclusion Diet (CDED) has emerged as a promising whole-food-based dietary intervention, specifically designed to reduce exposure to dietary components that impair the intestinal barrier and alter the gut microbiome. In a pivotal 12-week prospective randomized trial, Levine et al. compared CDED combined with partial enteral nutrition (PEN) to exclusive enteral nutrition (EEN) in children with mild to moderate CD [12]. The study showed that CDED + PEN was significantly better tolerated than EEN (97.5% vs. 73.6%, *p* = 0.002), and while both approaches achieved comparable remission rates at week 6, sustained corticosteroid-free remission at week 12 was notably higher in the CDED + PEN group (75.6% vs. 45.1%, *p* = 0.01) [14]. Additionally, the CDED + PEN group exhibited sustained reductions in inflammatory biomarkers and favorable modulation of the fecal microbiota [12]. These findings support the clinical utility of CDED + PEN as a more tolerable and effective strategy for inducing and maintaining remission in pediatric CD. Recent clinical data on adult patients reinforce the efficacy of CDED beyond pediatric populations. In a study involving 32 participants (18 women and 14 men), clinical remission was achieved in 76.7% of patients at 6 weeks and in 82.1% at 12 weeks of therapy [11]. Furthermore, fecal calprotectin levels showed a significant reduction by the second follow-up time point compared with baseline (*p* = 0.021) [11]. These findings suggest that CDED is also an effective therapeutic option for inducing remission in adult patients with CD.

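### Sections 2.5 and 2.6 end outcome collection for participants withdrawn for non-compliance or a serious deviation, so later outcomes can be missing in a way that depends on arm and outcome

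*Protocol article*

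**What the plan says.** Section 2.5 gives the investigator the right to "withdraw a subject from the study if it is determined that the subject can no longer comply with all study requirements". This is a discretionary power, and it concerns leaving the study, not only stopping the diet. The section also says "Subjects who withdraw from the study will not undergo further follow-up and will not be replaced". Its closing sentence keeps earlier data ("Data collected up to the point of withdrawal will be retained and included in the analysis") but adds that "no additional data will be gathered from the subject following withdrawal", with no distinction by reason for withdrawal.

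Section 2.6 lists grounds on which subjects will be withdrawn. One of them is "A protocol deviation that compromises the interpretation of the study results and the scientific validity of the study".

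The compliance burden differs by arm. Section 2.12 states: "Patients in the intervention group will be required to maintain this dietary strategy for 12 weeks". Table 2 sets out that arm's obligatory, permitted and prohibited foods for each phase, and enteral formula is taken as well. Section 2.10 gives controls a Mediterranean diet with a "balanced nutritional intake without unnecessary food restrictions". Section 2.12 also says that patients, research staff and medical staff are unblinded; only imaging assessors and laboratory analysts are blinded.

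**The concern.** Nothing in 2.5 or 2.6 separates stopping the diet from leaving the study. A participant who cannot keep to the diet, but who still consents to be seen, can lose every remaining outcome visit on the decision of someone who knows the allocation. Keeping the data up to that point does not supply remission status or body composition at a later visit.

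If such withdrawals are more common in one arm, and if those withdrawn would have fared differently from those who stay, the participants with data at week 12, 24 or 48 are no longer the groups that randomisation formed. This is a rule about what is collected. An analysis plan can impute missing outcomes or assign them a value, but it cannot recover what the protocol says will not be gathered. The limitations paragraph of the Discussion treats attrition only as a loss of power, not as a possible source of bias.

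**Working it through.** **The plan's own figure.** Section 2.11 gives 48 per group, a 5% dropout allowance and a target of 50–55. 48/(1 − 0.05) = 50.5, so 51 per group, which lies inside the stated range. The inflation reproduces. The 48 itself cannot be checked, because no endpoint, rates or effect size are given.

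**Inputs for the illustration.** The documents give no withdrawal rates by arm, so these are assumptions:
- true remission p = 60% in both arms (no diet effect);
- withdrawn in control w_C = 5% (equal to the planned dropout);
- withdrawn on the diet w_E = 10%, 12.5% or 20%;
- remission q among those withdrawn, had they been followed, 0% to 20%;
- 55 randomised per group (top of the stated range), two-sided 0.05, normal approximation with unpooled variance.

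The 12.5% has a loose anchor. The Discussion cites an adult study of 32 participants in which "clinical remission was achieved in 76.7% of patients at 6 weeks and in 82.1% at 12 weeks of therapy". With at most 32 in the denominator, 82.1% can only be 23/28, which leaves 4/32 = 12.5% without a week-12 result. The reason is not given.

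**Formula.** Remission among those still observed = (p − w·q)/(1 − w).

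Control: q = 0 gives 0.60/0.95 = 63.2%; q = 0.2 gives (0.60 − 0.01)/0.95 = 62.1%.

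| Withdrawn on diet | q | Diet, observed | Control, observed | False difference | Type I error |
|---|---|---|---|---|---|
| 10% | 0 | 66.7% | 63.2% | +3.5 points | 6.6% |
| 10% | 20% | 64.4% | 62.1% | +2.3 points | 5.7% |
| 12.5% | 0 | 68.6% | 63.2% | +5.4 points | 8.8% |
| 12.5% | 20% | 65.7% | 62.1% | +3.6 points | 6.6% |
| 20% | 0 | 75.0% | 63.2% | +11.8 points | 24.5% |
| 20% | 20% | 70.0% | 62.1% | +7.9 points | 13.0% |

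**When the bias vanishes or reverses.**
- q = 60%, so withdrawal is unrelated to outcome: both arms show 60% and the difference is 0.
- Equal withdrawal and equal q in both arms: the difference is 0.
- Those withdrawn do better than average: at 20% withdrawn and q = 80%, diet (0.60 − 0.16)/0.80 = 55.0% v control (0.60 − 0.04)/0.95 = 58.9%, so −3.9 points.
- Those withdrawn count as non-remitters: the difference is −(w_E − w_C)·q. This is 0 at q = 0. At q = 20% it is −1.0, −1.5 and −3.0 points for 10%, 12.5% and 20% withdrawn on the diet.

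**Another base rate.** With 45.1% remission in both arms (the comparator rate in the paediatric trial cited in the Discussion) and 30% v 5% withdrawn, q = 0 gives 0.451/0.70 − 0.451/0.95 = 64.4% − 47.5% = +17.0 points (unrounded rates). At q = 80% it gives (0.451 − 0.24)/0.70 − (0.451 − 0.04)/0.95 = 30.1% − 43.3% = −13.1 points (unrounded rates). The sign depends on quantities that the documents do not state.

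**The case against.** The strongest reply is that the protocol is milder than it may look. Withdrawal for non-compliance is a right, not a duty. Mandatory withdrawal covers only deviations serious enough to compromise interpretation and validity, and no section makes a dietary lapse a trigger. The Discussion lists varying adherence as a limitation, which suggests that imperfect adherers are expected to stay. Data before withdrawal are kept. The handling of missing outcomes may be set out in an analysis plan that is not shown. All of this stands, and it limits how many participants are affected. It does not remove the rule that, once someone is withdrawn for these reasons, nothing more is collected. It might also be said that the sentence on no further follow-up concerns those who leave by choice, but the closing sentence of 2.5 follows directly on investigator-led withdrawal and makes no such distinction.

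A reader might infer that the remission comparison is made among compliers and so favours the exclusion diet. The documents do not support that. It needs more withdrawal in the diet arm, worse outcomes in those withdrawn, and an analysis that drops missing outcomes; none of these is stated. If the last value were carried forward, a participant withdrawn before week 6 would keep the entry Harvey–Bradshaw score above 4 and count as not in remission, which could work against the diet.

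A reader might also take the cited adult study as proof of size: 76.7% can only be 23/30 and 82.1% only 23/28, against 23/32 = 71.9% over all enrolled, so the completer figure seems 10 points too high. Equal counts do not show that these are the same 23 people. The 10 points also assume that all four missing patients failed, and the study as described has no comparator. It shows how a shrinking denominator can lift a rate, not a bias between arms.

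Finally, 20% v 5% is an upper scenario. The plan expects 5% dropout, and the cited paediatric trial reports 97.5% tolerance of the diet, in a different population. The type I errors above use the 0.05 threshold; the Bonferroni correction in 2.15 would lower them but would leave the bias in the estimate unchanged.

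**Conclusion.** The point holds as a flaw in the data-collection rule of 2.5 and 2.6. Withdrawal for non-compliance or a serious deviation ends outcome collection, in an open-label trial where one arm is much harder to comply with. Later remission and body-composition data can then be missing in a way that depends on arm and outcome, and observed data could not show how far this has shifted the result.

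The direction is uncertain. Bias towards the diet is plausible under an observed-case analysis. Under the stated assumptions the false difference is about 2–3.5, 4–5 or 8–12 points for 10%, 12.5% or 20% withdrawn on the diet, with type I error of about 6–7%, 7–9% or 13–25%. At the lower withdrawal rates the effect is modest; at 20% it could decide a trial of this size. The choice of missing-data method and of a per-protocol set can properly sit in the analysis plan and is not part of this point.

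**What to change.** In 2.5 and 2.6, define stopping the assigned diet separately from leaving the study. Remove non-compliance and protocol deviation as reasons to end follow-up. State that every randomised participant who still consents stays on the 6, 12, 24 and 48 week visits and is analysed in the assigned arm. Withdrawal of consent and true loss to follow-up remain the reasons for having no later data. Record the reason for, and date of, each diet discontinuation and each study withdrawal, by arm.

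Clinical decisions about the diet itself are unchanged. The cost is protocol wording, the approval it needs, and visits already in Table 1 for the few participants who would otherwise be removed. The downside is a possibly diluted effect estimate, because participants who stopped the diet stay in their arm. The change should be made before anyone is withdrawn under the present rule, since outcomes not collected cannot be recovered.

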### 2.6. Withdrawal Criteria

Subjects will be withdrawn from this study if any of the following criteria are met:The occurrence of an adverse event which, in the judgment of the investigator, necessitates the withdrawal of the subject.A protocol deviation that compromises the interpretation of the study results and the scientific validity of the study.The voluntary decision of the subject.The explicit refusal of the subject to continue his/her participation in the study.Loss to follow-up.

### 2.7. Consent

Before any study-specific tests or procedures are performed, patients who meet the participation criteria (or their witness or legal representative) will be asked to sign the informed consent document approved by the Ethics Committee. They will be given sufficient time to review the informed consent document and have their questions answered before signing.

Each individual will be informed both orally and in writing about the study methodology, as well as about the potential adverse effects that may occur as a result of the various assessments to be carried out. Similarly, they will be informed that participation in the study is voluntary, both in terms of joining the study and of withdrawing from it at any time. In addition, all participants will be made aware of the characteristics of the products they will be consuming and the possible adverse effects that may occur during their use. Each participant will sign an informed consent form for participation in the project and an additional one for each stress test performed.

### 2.8. Research Ethics Approval

This study will be carried out in the HCUVA in accordance with the current Spanish legislation that regulates the carrying out of biomedical research projects, for which this protocol is established as a reference document for review by the Ethical Committees, as well as for the practical decision-making in the management of included patients by participating researchers.

### 2.9. Protocol Amendments

Except for those emergency situations, no protocol changes or deviations will be allowed without documented approval. The Research Ethics Committee must be informed of possible changes and will approve in writing any change or deviation that may increase the risks of the subject and/or may adversely affect the rights of the volunteer or the validity of the research. This stipulation does not apply to those changes that are made to reduce the inconvenience or avoid risks to the subjects and to changes that would affect the administrative aspects of the study. This study will be conducted respecting the rules of Good Clinical Practice (GCP) and the regulations and recommendations that appear in the Declaration of Helsinki and that are included in the current legislation on biomedical research at all times.

### 2.10. Intervention

Upon consenting to participate, patients will be randomized into two study arms based on the intervention administered:Control Group: Patients will receive modifications to their pharmacological treatment alongside standard nutritional recommendations. The control group will follow a Mediterranean diet with increased caloric and protein intake during the acute flare. The diet will emphasize a balanced nutritional intake without unnecessary food restrictions, along with adequate fiber and hydration (as tolerated), and a reduction in ultra-processed food consumption.Experimental Group: Patients will receive modifications to their pharmacological treatment and will be assigned to an intervention consisting of an exclusion diet in conjunction with supplemental enteral nutrition. This nutritional strategy will involve a progressive increase in the caloric intake derived from the diet, coupled with a corresponding reduction in supplemental enteral nutrition.

Prior to initiating the nutritional intervention—and subsequently at 6 and 12 weeks after the onset of the diet—alterations in body composition and functionality will be evaluated through anthropometric measurements and biochemical parameters pertinent to both the underlying pathology and the overall health status of the patient. Comprehensive functional assessments, including dynamometry and additional analyses such as BIA and nutritional ultrasound, will be conducted. Furthermore, a detailed nutritional and morphofunctional evaluation will be performed 24 and 48 weeks after the initiation of the exclusion diet [Figure 1].

Baseline biological samples (blood, urine, and stool specimens) will be collected before the start of the nutritional intervention. During the intervention, additional collections will occur at the 6-, 12-, 24-week visits, with a final sample collection at 48 weeks. A detailed assessment schedule can be found in Table 1.

### 2.11. Sample Size and Recruitment

Based on similar studies conducted primarily in pediatric populations, but also in adults [11,12], and taking into account the multiple outcomes to be obtained from the analysis of multiple variables, we estimate that, to achieve a significance level of 0.05 and a statistical power (β) of 0.8, a sample size of 48 patients per group would be required. Adjusting for a 5% dropout rate, we plan to recruit at least 50–55 patients per group to ensure the robustness of the analysis.

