## 2. Materials and Methods

### 2.1. Study Objectives

The primary objective of this clinical study is to determine the effectiveness and impact on body composition of implementing an ED for symptomatic remission in adult patients with active CD.

To achieve this objective, five specific aims are defined:To assess the improvement of clinical and inflammatory parameters related to the progression of the disease.To evaluate the incidence of sarcopenia through the assessment of muscle strength, function, and composition using functional tests, dynamometry, bioelectrical impedance analysis (BIA), and nutritional ultrasound.To determine the rate of improvement in the quality of life of patients and the disease remission by evaluating the Crohn’s Disease Activity Index (using the CVEII9 quality of life questionnaire and the Harvey–Bradshaw Index).To analyze the modifications in the intestinal microbiota resulting from the implementation of the ED.To examine the progression of clinical, anthropometric, analytical, and body composition parameters.

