### 2.15. Statistical Methods

All statistical analyses will be performed using SPSS software version 22.0, considering *p* < 0.05 as the threshold for statistical significance. A descriptive analysis of the variables will be conducted, providing point estimates and 95% confidence intervals. Continuous variables will be expressed as means and standard deviations or medians depending on the distribution of the data. Categorical variables will be reported as frequencies and percentages.

Comparisons of continuous variables will be performed using Student’s *t*-test (for two-group comparisons) or ANOVA (for comparisons involving more than two groups). Associations between categorical variables will be assessed using the chi-square test. Correlation analyses will be conducted using Pearson’s or Spearman’s correlation coefficients, depending on the normality of the variables under study. Relationships between multiple variables will be analyzed using multivariate statistical models.

Given the multiple outcomes to be assessed and the multiple comparisons to be analyzed, a Bonferroni correction (0.05/no. of comparisons as the significance level) will be also performed to avoid the risk of false positives.

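### The 80% power in section 2.11 is stated at 0.05, but section 2.15 also applies 0.05 divided by an unstated number of comparisons, so the stated power does not carry over to the corrected threshold

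*Protocol article*

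**What the plan says.** All references are to the protocol article.

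- **Section 2.11** gives one significance level and one power for the sample size: "a significance level of 0.05 and a statistical power (β) of 0.8, a sample size of 48 patients per group", with 50–55 recruited to cover 5% dropout. The same sentence says the estimate was made "taking into account the multiple outcomes to be obtained from the analysis of multiple variables". It names no endpoint, effect, number of comparisons or divided alpha.
- **Section 2.15** first sets p < 0.05 "as the threshold for statistical significance" for all analyses. It then says that, because of the multiple outcomes and comparisons, "a Bonferroni correction (0.05/no. of comparisons as the significance level) will be also performed to avoid the risk of false positives". No test is exempt, and the number of comparisons is not given.
- **Section 2.1** does not single out one test: "The primary objective of this clinical study is to determine the effectiveness and impact on body composition" of the exclusion diet for symptomatic remission, followed by five specific aims.
- **Section 2.13.1** defines clinical remission (Harvey–Bradshaw score below 5, and calprotectin below 250 µg/g) but does not call it primary or attach a primary time point.

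**The concern.** The alpha that sizes a trial should be the alpha at which its main result is judged. Here the sizing alpha is 0.05, while one of the two analysis thresholds is 0.05/m with m open. A stricter threshold with the same patients and the same effect means lower power, so the 80% in 2.11 cannot be read across to a Bonferroni-corrected result.

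Two things are at stake. A real effect may miss the corrected threshold more often than 2.11 leads the reader to expect. And a p-value between 0.05/m and 0.05 is significant under one sentence of 2.15 and not significant under another. With m unstated and no test set apart, that choice could be made after the data are seen, in a trial where patients and study staff are not blinded (2.12).

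**Working it through.** **Inputs.** From 2.11: 48 per group, alpha 0.05, power 0.80, 5% dropout, 50–55 recruited. From 2.12: 1:1 allocation. From section 3 (Discussion): 75.6% v 45.1% corticosteroid-free remission at week 12 in a paediatric trial. Assumed: two-sided tests, and the values of m.

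**Step 1: can 48 be reproduced?** Not directly, because 2.11 gives no endpoint or effect. The dropout step is consistent: 48/0.95 = 50.5, so 51, which lies within 50–55. Two readings of the 48 are therefore carried forward.

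**Step 2, reading A: 48 per group gives 80% at two-sided 0.05.** The implied standardised difference, by normal approximation, is d = (z₀.₉₇₅ + z₀.₈₀)·√(2/n) = (1.960 + 0.842)·√(2/48) = 0.572. The two-sample t-test gives d = 0.578, which is used below. Power at the divided level is approximately Φ(d·√(n/2) − z₁₋₀.₀₂₅/ₘ). For m = 5 the approximation gives Φ(0.572 × 4.899 − 2.576) = Φ(0.226) = 59%; the t-test gives 58%.

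**Step 3, reading B: the Discussion rates.** Power = Φ{[Δ√n − z·√(2p̄(1−p̄))] / √(p₁q₁ + p₂q₂)}, where Δ = 0.305, p̄ = 0.6035, √(2 × 0.6035 × 0.3965) = 0.692, √(0.756 × 0.244 + 0.451 × 0.549) = 0.657 and Δ√48 = 2.113.

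- m = 1: (2.113 − 1.960 × 0.692)/0.657 = 1.15, power 88%
- m = 2: (2.113 − 2.241 × 0.692)/0.657 = 0.86, power 80%
- m = 3: (2.113 − 2.394 × 0.692)/0.657 = 0.70, power 76%

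**Step 4: results per comparison.**

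| m (assumed) | Alpha | A: power at 48 per group | A: n per group for 80% | B: power at 48 per group | B: n per group for 80% |
|---|---|---|---|---|---|
| 1 | 0.05 | 80% | 48 | 88% | 40 |
| 2 | 0.025 | 71% | 59 | 80% | 48 |
| 3 | 0.0167 | 65% | 65 | 76% | 53 |
| 5 | 0.01 | 58% | 72 | 69% | 59 |
| 20 | 0.0025 | 40% | 92 | 51% | 76 |

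For scale, m = 5 would be one comparison per specific aim, and m = 20 would be five aims at four follow-up visits. Neither count is stated in the article.

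**Step 5: does the upper recruitment limit help?** With 55 evaluable per group and no losses, reading A gives 77% at m = 2 and 66% at m = 5. Reading B gives 82% at m = 3 and 77% at m = 5. After the planned 5% dropout, 55 becomes about 52 evaluable (55 × 0.95 = 52.25).

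**The case against.** Several points on the other side carry weight.

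- **A reader might infer that 48 is a single-test size with no room for any division of alpha.** The document does not support that. Section 2.11 says multiple outcomes were considered. On the Discussion rates one test at 0.05 needs only 40 per group, and 0.05/2 needs exactly 48. A two-comparison allowance fits the printed number at least as well as a single test. Nothing shows that the authors calculated it this way, but it cannot be ruled out.
- **A reader might infer that no outcome has the stated power.** That cannot be shown either, because neither the effect nor m is given. On reading B, 80% holds at m = 2, and with 55 evaluable per group it holds at m = 3.
- **Large values of m are assumptions.** The long list of serum parameters in 2.13.3 says what will be measured. It does not define a family of tests, so a count of parameters times visits should not be presented as the plan's m.
- **The Discussion rates are borrowed.** They come from children, with exclusive enteral nutrition as comparator and a different remission definition, and 2.11 does not tie its calculation to them.
- **The correction may be meant as a companion analysis.** Section 2.15 says it is also performed, which could mean that it is reported beside the nominal result. A condensed article may also leave the comparison family to a fuller plan.

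What stands is a mismatch in the printed text: the sizing level is 0.05, and 2.15 calls 0.05/m the significance level while keeping p < 0.05. If the correction is only a companion analysis, the article still does not say which result decides.

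**Conclusion.** The point holds in a bounded form. The 80% in 2.11 is attached to 0.05 and to no identified test, and it does not apply at the Bonferroni threshold in 2.15. Two significance rules coexist, and the text does not say which governs. At 48 per group, power per comparison falls below 80% from m = 2 if the trial was sized at an undivided 0.05, and from m = 3 if the Discussion rates apply. Three or more comparisons therefore lose it under both readings. At m = 5 the range is 58% to 69%, and at m = 20 it is 40% to 51%. These figures rest on two-sided tests, on assumed values of m, and on either a back-solved effect or borrowed rates. They do not show that 48 was miscalculated. The matter goes beyond missing detail because it affects which results the trial may call significant.

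**What to change.** In 2.11 and 2.15:

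1. Name one primary outcome and time point, tested at two-sided 0.05 outside the Bonferroni family. Clinical remission by the 2.13.1 rule at week 12 is one example, and its data are already scheduled in Table 1. The choice belongs to the sponsor, since 2.1 also gives body composition a place in the primary objective.
2. Restate the 48 per group as the effect it detects for that test, using the sponsor's own assumed effect, and drop or substantiate the statement that multiple outcomes were allowed for. In the same sentence, correct the label: power is 1 − β, not β.
3. Limit Holm or Bonferroni control to a short, listed set of secondary comparisons, label the rest exploratory, and remove the free-standing p < 0.05 rule for those outcomes.

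Alternatively, keep Bonferroni over all comparisons, state m, say that it is the deciding rule, and restate the power it gives at 48 per group.

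The cost is wording only, with no extra patients. The downside of the first route is that other outcomes, possibly including body composition, become secondary or exploratory. The downside of the second is a less favourable stated power.
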